[figure not shown][figure not shown]

---

## STUDY SYNOPSIS

---

**Clinical Trial Identifier:** JAIVAC-1\_1\_09

---

**Study Title:** A Phase I, Randomised, Controlled, Dose-escalating, Single-blind Clinical Trial to Evaluate the Safety and Immunogenicity of the JAIVAC-1 Vaccine (PfMSP-119 and PfF2) formulated with Montanide ISA 720 in healthy Indian male subjects between 18 to 45 years of age.

---

**Sponsors (Legal Names):** 1. European Vaccine Initiative (EVI), Heidelberg, Germany.  
International Centre for Genetic Engineering and Biotechnology (ICGEB), New Delhi, India

---

**Biological Evaluator(s):** [name], ICGEB

---

**Contract Research Organisation:** DiagnoSearch Life Sciences Pvt. Ltd. (DLS),  
Mumbai, Maharashtra, India

---

**Study Site:** Lotus Labs Pvt. Ltd.  
[name]  
[name]

---

**Principal Investigator:** [name]  
Lotus Labs Pvt Ltd  
[name]  
[name]

---

**Clinical Development Phase:** Phase I (first study in humans)

---

**Name of the Investigational Vaccine:** JAIVAC-1 *Plasmodium falciparum* malaria vaccine formulated with Montanide ISA 720 (JAIVAC-1 – Montanide ISA 720)

---

**Active Ingredient(s) of the Investigational Vaccine:** PfMSP-119 and PfF2

---

*Information contained in this publication is the property of EVI and ICGEB and is confidential and will not be disclosed to third parties without written authorization from EVI and ICGEB. No part of this document may be reproduced, stored in a retrieval system or transmitted in any form or by any means -electronic, mechanical, recording or otherwise - without the prior authorization of EVI and ICGEB*

[figure not shown][figure not shown]

**Dose(s) of the Investigational Vaccine:**

The three (3) dosages of antigen of the investigational vaccine to be evaluated in the present study include:

- 10 µg of each antigen (PfMSP-119 and PfF2), 0.1 ml of the reconstituted and emulsified (JAIVAC-1 – Montanide ISA 720) vaccine (**Dosage A**)
- 25 µg of each antigen (PfMSP-119 and PfF2), 0.25 ml of the reconstituted and emulsified (JAIVAC-1 – Montanide ISA 720) vaccine (**Dosage B**)
- 50 µg of each antigen (PfMSP-119 and PfF2), 0.5 ml of the reconstituted and emulsified (JAIVAC-1 – Montanide ISA 720) vaccine (**Dosage C**)

**Name of the Adjuvant:**

Montanide ISA 720

**Name of the Comparator Vaccine:** Hepatitis B vaccine

**Vaccination Schedule:**

All subjects will receive three (3) doses of the assigned investigational vaccine or control vaccine on Days 0, 28 and 180 by intramuscular route. Follow-up duration is 365 days/ one (1) year after the first administration of the vaccine.

**Study Indication:**

Recombinant vaccine for *Plasmodium falciparum* malaria

**Primary Objective(s):**

- To evaluate the safety of three different dosages of JAIVAC-1 malaria vaccine (PfMSP-119 and PfF2) formulated with Montanide ISA 720 as adjuvant in healthy Indian male subjects between 18 to 45 years of age
- To compare the safety of three different dosages of JAIVAC-1 vaccine (PfMSP-119 and PfF2) formulated with Montanide ISA 720 as adjuvant to the safety of the control vaccine (Hepatitis B vaccine) in healthy Indian male subjects between 18 to 45 years of age

**Secondary Objective(s):**

- To assess the humoral response to the vaccine antigens PfMSP-119 and PfF2 by measuring the IgG antibody response by Enzyme Linked Immunosorbent Assay (ELISA) in healthy Indian male subjects between 18 to 45 years of age
- To assess the humoral response to the vaccine antigens PfMSP-119 and PfF2 by measuring the IgG antibody response by Immunofluorescence Assay (IFA) in healthy Indian male subjects between 18 to 45 years of age

Information contained in this publication is the property of EVI and ICGEB and is confidential and will not be disclosed to third parties without written authorization from EVI and ICGEB. No part of this document may be reproduced, stored in a retrieval system or transmitted in any form or by any means -electronic, mechanical, recording or otherwise - without the prior authorization of EVI and ICGEB

[figure not shown][figure not shown]

---

**Exploratory Objective(s):**

- To assess the quality of the humoral immune response (IgG antibody) to the vaccine antigens in healthy Indian male subjects by measuring the following:
    - Subclasses of IgG antibodies - IgG1, IgG2, IgG3, IgG4 by ELISA
    - The ability of the IgG antibodies to block homologous and heterologous parasite growth *in vitro* by a *P. falciparum* blood-stage growth inhibition assay (GIA) against three parasite strains
- 

*Information contained in this publication is the property of EVI and ICGEB and is confidential and will not be disclosed to third parties without written authorization from EVI and ICGEB. No part of this document may be reproduced, stored in a retrieval system or transmitted in any form or by any means -electronic, mechanical, recording or otherwise - without the prior authorization of EVI and ICGEB*

---

### Study Design:

The present study is designed as a randomised, controlled, single-blind and dose-escalating clinical study for the assessment of the safety and immunogenicity of JAIVAC-1 malaria vaccine (PfMSP-119 and PfF2) formulated with Montanide ISA 720 as adjuvant in healthy Indian male subjects between 18 to 45 years of age. This is a dose-escalating study and involves testing of three (3) different dosages of JAIVAC-1 malaria vaccine (PfMSP-119 and PfF2) formulated with Montanide ISA 720 as adjuvant with the intramuscular administration of the investigational vaccine as a 3-dose schedule on Days 0, 28 and 180.

30 subjects will receive JAIVAC-1—Montanide ISA720 (10 subjects at each dosage cohort) and 15 subjects will receive control vaccine, Hepatitis B vaccine (5 subjects at each dosage cohort). Dosing of the JAIVAC-1—Montanide ISA720 vaccine arms will begin with Cohort 1 (i.e. 0.1 ml of investigational vaccine administered by intramuscular route – Dosage A), followed by Cohort 2 (i.e. 0.25 ml of investigational vaccine – Dosage B) and finally Cohort 3 (i.e. 0.5 ml of investigational vaccine – Dosage C). Each cohort will be staggered into sub-cohorts such that the subjects in each cohort will be enrolled over a three-day period. The first three (3) subjects of the first dose (Cohort 1) will be kept under observation for 24 hrs following vaccination. The decision of the 24-hour housing for the remaining subjects will be jointly taken by the Principal Investigator and Medical and Safety Monitor, DLS.

An independent Data Safety Monitoring Board (DSMB) will be appointed for this study. Dose escalation to the next higher dosage cohort of JAIVAC-1 – Montanide ISA 720 will occur after the safety data from the first dose of vaccine through Day 14 day for all 15 subjects of the previous dosage cohort has been reviewed by the DSMB comprising of three (3) independent clinicians with relevant expertise in the field of vaccines development and evaluation of vaccine safety along with the designated Local Safety Monitor (who would be a designated personnel from the investigational site but independent of the study team).

Thus, for each dosage cohort, each subject will receive a total of three (3) doses of either of the study or control vaccines by intramuscular route, one each on Day 0, Day 28 and Day 180 respectively.

---

## Dosing Cohorts:

There will be three (3) cohorts in this study such that each cohort will consist of 15 eligible subjects randomised in a ratio of 2:1 as follows:

### Cohort 1

|                      |                                                                                                                                                                                                                                        |
|----------------------|----------------------------------------------------------------------------------------------------------------------------------------------------------------------------------------------------------------------------------------|
| Test Arm 1    | 10 subjects shall receive dosage A of investigational vaccine (0.1 ml of JAIVAC-1 vaccine containing 10µg PfMSP-1 19 and 10µg PfF2 formulated with adjuvant Montanide ISA 720) by intramuscular route on Days 0, 28 and 180 |
| Control Arm 1 | 5 subjects shall receive control vaccine (1 ml of Hepatitis B vaccine) by intramuscular route on Days 0, 28 and 180                                                                                                                    |

### Cohort 2

|                      |                                                                                                                                                                                                                                         |
|----------------------|-----------------------------------------------------------------------------------------------------------------------------------------------------------------------------------------------------------------------------------------|
| Test Arm 2    | 10 subjects shall receive dosage B of investigational vaccine (0.25 ml of JAIVAC-1 vaccine containing 25µg PfMSP-1 19 and 25µg PfF2 formulated with adjuvant Montanide ISA 720) by intramuscular route on Days 0, 28 and 180 |
| Control Arm 2 | 5 subjects shall receive control vaccine (1 ml of Hepatitis B vaccine ) by intramuscular route on Days 0, 28 and 180                                                                                                                    |

### Cohort 3

|                      |                                                                                                                                                                                                                                        |
|----------------------|----------------------------------------------------------------------------------------------------------------------------------------------------------------------------------------------------------------------------------------|
| Test Arm 3    | 10 subjects shall receive dosage C of investigational vaccine (0.5 ml of JAIVAC-1 vaccine containing 50µg PfMSP-1 19 and 50µg PfF2 formulated with adjuvant Montanide ISA 720) by intramuscular route on Days 0, 28 and 180 |
| Control Arm 3 | 5 subjects shall receive control vaccine (1 ml of Hepatitis B vaccine) by intramuscular route on Days 0, 28 and 180                                                                                                                    |

*Information contained in this publication is the property of EVI and ICGEB and is confidential and will not be disclosed to third parties without written authorization from EVI and ICGEB. No part of this document may be reproduced, stored in a retrieval system or transmitted in any form or by any means -electronic, mechanical, recording or otherwise - without the prior authorization of EVI and ICGEB*

[figure not shown][figure not shown]

---

**Number of Subjects:**

A sufficient number of subjects will be screened to enrol a total number of 45 subjects in the study.

- 30 subjects will receive the investigational vaccine (i.e. JAIVAC-1 – Montanide ISA 720) with ten (10) subjects in each dosage cohort and
- 15 subjects will receive the control vaccine (i.e. Hepatitis B vaccine) with five (5) subjects in each dosage cohort.

Subjects who are discontinued from the study following administration of the first dose of the assigned vaccine will be considered as drop-outs and will not be subsequently replaced.

---

**Inclusion Criteria**

1. Male subject aged 18 to 45 years (both inclusive)
  2. Subject with general good health based on the medical history and clinical examination
  3. Subject must be willing to sign the Informed Consent Form
  4. Subject must be reachable by phone during the entire study period (12 months)
  5. Subject must be capable and willing to complete and return diary cards and to attend all follow-up visits
  6. Male subject must agree to use one of the following medically-acceptable birth control measures throughout the duration of the study (birth control counselling and measures will be provided by sites as required)
    - Double barrier method (e.g. condom with spermicidal jelly) used for the entire study period
    - Or
    - Should be Surgically sterile (vasectomy)
- 

*Information contained in this publication is the property of EVI and ICGEB and is confidential and will not be disclosed to third parties without written authorization from EVI and ICGEB. No part of this document may be reproduced, stored in a retrieval system or transmitted in any form or by any means -electronic, mechanical, recording or otherwise - without the prior authorization of EVI and ICGEB*

---

**Exclusion Criteria:**

1. Subject with evidence of IgG antibodies against PfMSP-119 and PfF2 as measured by ELISA
  2. Subject with prior history of immunisation with Hepatitis B vaccine
  3. Subject with known history of malaria
  4. Subject with history of allergic reactions, hypersensitivity or anaphylaxis to any of the components of the study vaccines (JAIVAC-1 – Montanide ISA 720 malaria vaccine or Hepatitis B vaccine) (including adjuvant or peptide) or with history of serious allergic reactions to any substance, requiring hospitalisation or emergency medical care
  5. Subject with previous vaccination with any other malaria candidate vaccines
  6. Subject with use of an investigational or non-registered drug or vaccine other than the study vaccines within three (3) months preceding the first study vaccination, or planned use during the entire clinical trial period
  7. Subject, who receives any vaccination or gamma globulin during the three-month period prior to the first vaccination
  8. Subject with chronic administration (defined as more than 14 days) of immuno-suppressants or other immune-modifying drugs within six months prior to the first vaccination. This includes any dose level of oral steroids or inhaled steroids, but not topical steroids
  9. Subjects will be excluded if AST > 40 IU/L, ALT > 41 IU/L,  $\gamma$  GT > 71 IU/L, Total Bilirubin > 1.2 mg/ dL, Indirect Bilirubin > 1.2 mg/ dL, Direct Bilirubin > 0.4 mg/dL, Serum Creatinine > 1.2 mg/ dL (Appendix B and B-1).
  10. Subjects will be excluded in case of out of range values for the following parameters: Hemoglobin 13 to 18 g/ dL, RBC count  $4.0$  to  $7.0 \times 10^6/\mu\text{L}$  TLC  $4.0$  to  $11.0 \times 10^3/\mu\text{L}$ , platelet count 150 to  $500 \times 10^3/\mu\text{L}$ , Neutrophils 40 to 75 % or Eosinophils > 10 %, Sodium 136 to 145 mEq/L, Potassium 3.5 to 5.1 mEq/L, Random Blood Glucose 45 to 130 mg/dl and Alkaline Phosphatase 40 to 129 U/L (Appendix B and B-1)
  11. Subjects with other clinically significant abnormal laboratory values based on the normal reference range (Refer Appendix B and B1) apart from the laboratory parameters listed above.
-

- 
12. Subject with positive HIV, HBV or HCV test
  13. Subject with positive direct Coomb's test
  14. Subject with a peripheral blood film/smear with features of haemolysis or any other haematological disorder
  15. Subject unable to give written informed consent
  16. Subject unable to be closely followed for social, geographic or psychological reasons
  17. Subject with previous history of drug or alcohol abuse interfering with normal social function during a period of one year prior to enrolment in the study or positive urine drug test
  18. Subject with an abnormal 12-lead ECG at screening associated with relevant clinical symptoms/signs suggestive of cardiac pathology (including conduction disturbances)
  19. Subject with an abnormal Chest X-Ray associated with relevant clinical symptoms/signs of respiratory pathology at screening/ anytime in the past 6 months
  20. Subject with known history of congenital/hereditary immunodeficiency disorders
  21. Subject with acute or chronic pulmonary, reticulo-endothelial, cardiovascular, hepatic, renal or neurological condition, or any other clinical findings that in the opinion of the clinical investigator, may increase the risk of participating in the study
  22. Subject with any other condition that in the opinion of the clinical investigator would jeopardise the safety or rights of a participant in the trial or would render the participant unable to comply with the protocol
-

[figure not shown][figure not shown]

---

**Planned duration of Study****Participation/Study period:**

The total duration of each subject's participation (excluding allowed window periods) will be approximately 386 days which includes:

- Pre-Screening Period of 7 days
- Screening period of 14 days
- Vaccination period of 180 days (refer window period by visit)
- Follow-up period till 365 days (1 year) after the first vaccination (window period of +/- 7 days)

The approximately, total study duration (476 days) includes enrolment period (90 days) and duration of participation of individual subjects (386 days).

---

*Information contained in this publication is the property of EVI and ICGEB and is confidential and will not be disclosed to third parties without written authorization from EVI and ICGEB. No part of this document may be reproduced, stored in a retrieval system or transmitted in any form or by any means -electronic, mechanical, recording or otherwise - without the prior authorization of EVI and ICGEB*

---

**Primary Endpoint(s)**

The safety profile will be assessed on the basis of the following criteria

- Immediate reactogenicity (any event occurring within the first three (3) hours after each vaccination, with emphasis on allergic reactions)
- Local and systemic reactogenicity (any event occurring from three (3) hours post vaccination on Day 0 till Day 14 after each dose)
- Any unsolicited adverse events 28 days after each vaccination
- Any Serious Adverse Event (SAE) occurring from the first dose of vaccine till the last follow-up visit.
- Biological safety, 28 days after each vaccination, in reference with the baseline before the first dose, by measuring the following parameters:
  - Haematology: RBC Count, Haemoglobin\*, Haematocrit/Packed Cell Volume (PCV), MCV (Mean Corpuscular Volume), MCH (Mean Corpuscular Haemoglobin), MCHC (Mean Corpuscular Haemoglobin Concentration) on Days -14, 28, 56, 180, 208, 365
  - Platelet Count and Total Leukocyte Count (TLC) along with Differential Leukocyte Count (DLC) on Days -14, 28, 56, 180, 208, 365.  
\*If the haemoglobin drops below 13 gm/dL, then a direct Coomb's test and a peripheral blood smear/film will be prepared and examined for evidence of possible haemolysis
  - Serum Chemistry: Potassium, Sodium, AST, ALT, Direct, Indirect and Total Bilirubin, Alkaline Phosphatase, Gamma Glutamyl Transpeptidase (γGT), Creatinine, and Random blood glucose on Days -14, 28, 56, 180, 208, 365

The Investigator will be responsible for causality assessment i.e. assessment of the relationship of the AE to either of the assigned the study vaccines, using the following definitions: related or not related.

---

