***Following are the footnotes for TABLE 1: PROTOCOL JAIVAC-1\_1\_09 - SCHEDULE OF VISITS AND PROCEDURES***

1. **Window Period:** A window period of specific number of days has been assigned for each visit. (*Refer Table 1 for details*). In case a subject cannot come on a scheduled day he can be called anytime in the window period for that particular visit but for subsequent visits he should be urged to adhere to the original visit schedule.
2. **Study Period:** The study consists of four (4) distinct study periods: A pre-screening period of 7 days, a screening period of 14 days, a vaccination period of 180 days and a follow-up period till 365 days from the first dose of the assigned study vaccines.
3. **Informed Consent:** There are two (2) discreet informed consent documents for this study. Following the signing of the pre-screening informed consent, blood sample for testing for anti-malarial antibodies will be taken. Only if the subject tests negative for anti-malarial antibodies, he will be administered the main informed consent form. Following the signing of the main informed consent, further study-related procedures will be undertaken.
4. **Screening number:** Following the signing of the pre-screening informed consent, each subject will be assigned a unique screening number. This same number will be used to identify the subject both during the pre-screening as well as the screening period.
5. **Demographics:** At the pre-screening Visit (Visit 1), each subject shall be required to provide demographic information (including date of birth, height, weight, gender, and race).
6. **ELISA for Anti-malarial Antibodies:** Blood sample drawn in the pre-screening period will be used for ELISA test for anti-malarial antibodies. Subjects with evidence of IgG antibodies against PfMSP-119 and PfF2 as measured by ELISA at pre-screening visit (Visit 1) will be not be further considered for the study.
7. **Vital Signs and 12-lead ECG:** General examination including vital signs i.e. temperature, pulse, respiratory rate (TPR) and blood pressure (supine BP) will be performed at every visit. One 12-lead ECG and one X-Ray Chest will be done at the screening visit (Visit 2).
8. **Birth Control Counselling:** The importance of strict adherence to the birth control measures during the study duration will be emphasised at these visits to the subjects.

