#### C. Vaccination Schedule

*Information contained in this publication is the property of EVI and ICGEB and is confidential and will not be disclosed to third parties without written authorization from EVI and ICGEB. No part of this document may be reproduced, stored in a retrieval system or transmitted in any form or by any means -electronic, mechanical, recording or otherwise - without the prior authorization of EVI and ICGEB*

[figure not shown][figure not shown]

The vaccine will be administered as per a 3-dose vaccination schedule on Days 0, 28 and 180

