### **7.2.2 Assessment of Local and Systemic Reactogenicity (Solicited AEs)**

Local and systemic reactogenicity will be assessed for a period of 14 days following each vaccination i.e. from Days 0 to 14 for the first dose, Day 28 to 42 for the second dose and Day 180 to 194 for the third dose of the assigned study vaccine. This assessment of local and systemic signs and symptoms will be done based both on the subject diary card and investigator assessment as follows:

- For the first 14 days the subjects will be asked to record the local and systemic signs and symptoms (Solicited AEs) in their diary cards (pre-printed).
- In addition, 14 days after each vaccination (i.e. on Days 14, 42 and 194), the investigator will do an independent assessment of the local and systemic signs and symptoms.

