### **Diary Cards**

Distribution: Pre-printed diary cards will be given to subject on the days of vaccine administration (Days 0, 28 and 180) and will be collected on Day 28 following each vaccination. Detailed instructions to fill the diary cards will be given to the subjects at the time of dispensing the diary. These diary cards will be used for the record of solicited AEs (local and systemic reactogenicity) till Day 14 and unsolicited AEs till Day 28 after each vaccination by the subject. Thus three (3) such diary cards will be given to each subject.

Review and Transcription: 7 and 14 days after each vaccination, i.e. on Days 7, 14, 35, 42, 187 and 194, the investigator will review the subject diary card and transcribe the local and systemic reactogenicity data and the unsolicited AEs from the subject diary cards into the CRF.

Collection: Pre-printed diary cards given to the subject on the days of vaccine administration (Days 0, 28 and 180) will be collected 28 days after each vaccination i.e. respectively on Days 28, 56 and 208.

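### Post-dose visits follow the original calendar rather than the actual dose date, so the 14-day assessment can fall at post-dose day 12 and diary collection and 28-day samples at day 26

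*Supplement*

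**What the plan says.** **Endpoints counted from the dose.** The synopsis (Primary Endpoint(s)) and section 4.6.1 define solicited reactogenicity up to Day 14 after each dose (synopsis: "any event occurring from three (3) hours post vaccination on Day 0 till Day 14 after each dose"). They define unsolicited events as "Any unsolicited adverse events 28 days after each vaccination", and biological safety at 28 days after each vaccination.

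**Visits on the calendar.** Doses are planned for Days 0, 28 and 180. Tables 1 and 7 give Visits 3 to 13 a window of ±1 day, including dosing Visits 3, 6 and 10. Visit 14 has ±7 days. Footnote 1 says that when a subject uses a window, "for subsequent visits he should be urged to adhere to the original visit schedule". No text ties a later visit to the actual dose date.

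**Assessments on fixed days.** The investigator's independent assessment is on Days 14, 42 and 194 (7.2.2.2). Diary cards "will be collected 28 days after each vaccination i.e. respectively on Days 28, 56 and 208" (7.4.2, Diary Cards). The laboratory and antibody samples that follow doses 2 and 3 by 28 days are drawn at the same visits, Days 56 and 208.

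**The solicited window, two ways.** Section 7.2.2 says "Local and systemic reactogenicity will be assessed for a period of 14 days following each vaccination" and then equates this with study days, "Day 28 to 42 for the second dose and Day 180 to 194 for the third dose". Section 7.2.2.1 repeats the equation.

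**The concern.** The two descriptions agree only if the dose and the later visit both fall on their nominal days. When a permitted shift is used, the interval since the dose changes, and nothing brings it back to 14 or 28 days.

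Completeness of the primary safety record is what is at stake. Section 10.6 makes the diary card the source for solicited and unsolicited events. If the card is taken back before day 28, the remaining days have no diary. The 28-day laboratory and antibody values would also not represent the same interval in every subject. In arms of 10 and 5, one missed event changes a rate by 1/10 = 10 or 1/5 = 20 percentage points, provided it was that subject's only event of its type.

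**Working it through.** **Inputs.** Dose days 0, 28, 180; 14-day assessments on Days 14, 42, 194; card collection on Days 28, 56, 208 (7.2.2.2; 7.4.2). Shifts of −1, 0 or +1 day for Visits 3 to 13 (Tables 1 and 7).

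**Formula.** Days since dose = (nominal visit day + visit shift) − (nominal dose day + dose shift).

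**The plan's own figures.** With no shift: 14 − 0 = 42 − 28 = 194 − 180 = 14, and 28 − 0 = 56 − 28 = 208 − 180 = 28. The stated intervals reproduce.

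**Dose 2 with permitted shifts** (days since dose):

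| Actual dose day | Assessment on Day 41 / 42 / 43 | Collection and samples on Day 55 / 56 / 57 |
|---|---|---|
| 27 | 14 / 15 / 16 | 28 / 29 / 30 |
| 28 | 13 / 14 / 15 | 27 / 28 / 29 |
| 29 | 12 / 13 / 14 | 26 / 27 / 28 |

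**Dose 3** has the same ranges: 193 − 181 = 12 and 207 − 181 = 26 at the earliest, 195 − 179 = 16 and 209 − 179 = 30 at the latest.

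**Dose 1.** If Day 0 is by definition the day of the first dose, collection falls at 27 to 29 days. Only if the Visit 3 window lets the dose fall on Day 1 is it 27 − 1 = 26.

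**Possible shortfall.** 28 − 26 = 2 days, or 2/28 = 7% of the unsolicited period.

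**What follows collection.**
- After dose 1, the second card is issued at the visit that collects the first, so recording continues.
- After dose 2, the next visit is nominally Day 180, which is 180 − 55 = 125 days after collection on Day 55. Tables 1 and 7 mark unsolicited AEs there.
- After dose 3, the next visit is nominally Day 365, which is 365 − 207 = 158 days after collection on Day 207 (151 to 165 with the ±7 window). Tables 1 and 7 do not mark unsolicited AEs there, and section 7.4.3.14 lists only SAEs.

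**Solicited window, two readings:**

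| Actual dose day | 14 days from the dose | Fixed days in 7.2.2 |
|---|---|---|
| 27 | 27–41 | 28–42 |
| 29 | 29–43 | 28–42 (ends at post-dose day 13) |
| 179 | 179–193 | 180–194 |
| 181 | 181–195 | 180–194 (ends at post-dose day 13) |

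**The case against.** Several stronger readings are tempting, and the documents do not support them.

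- **That the 28-day AE window itself closes at day 26.** It does not. The unsolicited window is counted from the dose in the endpoints (4.6.1), the diary text (7.2.3, 7.4.2), reporting (8.4.2) and analysis (11.5.1.3). Only the collection visit can fall at day 26.
- **That an early dose loses its own first day.** A dose on Day 27 or 179 precedes the fixed window in 7.2.2, but footnote 17 counts solicited events from vaccination, the card is issued on the day of the dose, and every subject is observed for three hours after each dose. What remains is a conflict of wording.
- **That both effects strike together.** The early-dose conflict and the day-26 collection need opposite dose shifts. After a Day 27 dose, collection falls at 28 to 30 days.
- **That a third of windows are short.** This would require all nine shift combinations to be equally likely. Footnote 1 reserves the window for a subject who cannot come on the scheduled day.

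Three further objections have force. First, the subject keeps the card until the 28-day visit, so an early 14-day visit moves the investigator's examination and does not stop the subject's own solicited recording. Second, event start dates (8.4.3) and injection dates (11.1.3) are recorded, so the separate SAP that section 11 announces can derive days since dose. It cannot supply days that were never collected. Third, section 8.1 requires AE enquiry at every visit, and SAEs are captured to Day 365. For non-serious events after dose 3, though, the enquiry relies on recall some five months after the Day 208 visit, so it is only a partial backstop.

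**Conclusion.** The point stands in a limited form. The endpoints promise 14 and 28 days after each dose. Under the permitted shifts, the investigator's assessment can fall at day 12 after doses 2 and 3, and card collection and the 28-day laboratory and antibody samples at day 26. For dose 1 the earliest collection is day 27 if Day 0 is the dose day. Up to two days of the 28-day unsolicited record can go uncollected, most clearly after dose 3. Separately, 7.2.2 and 7.2.2.1 contradict themselves whenever dose 2 or 3 is off its nominal day.

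The effect is one to two days in a descriptive study of 45 subjects with no hypothesis tests. How often it would occur cannot be stated from the documents. The conclusion assumes that the windows are used to their limits and that sites follow footnote 1, which urges rather than requires a return to the calendar. It merits correction because it touches the primary safety record, later analysis cannot restore missing diary days, and the remedy is nearly free.

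**What to change.** 1. In Tables 1 and 7 and footnote 1, count the non-dosing post-dose visits (Visits 4–5, 7–9 and 11–13) from the actual date of the preceding dose.
2. Let the 14-day assessments (Visits 5, 8 and 12) and the card collection at Visits 9 and 13 be on time or late, but not early. If the present one-day tolerance is kept on the late side only, they fall at 14 to 15 and 28 to 29 days after the dose.
3. Restate the solicited windows in 7.2.2 and 7.2.2.1 as days since the actual dose.
4. Leave the dosing days and the dosing-visit windows as they are. The sponsor should reconcile the ±1 day at Visit 3 with Day 0 being the day of the first dose.

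The cost is wording and slightly less scheduling freedom. No visits, samples or subjects are added. Card 1 is still collected at Visit 6, a dosing visit, so its collection may remain a day early; the second card, issued that day, limits the consequence.
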